## Methods and Analysis

### Setting, Participant Recruitment, and Eligibility Criteria

The study will be conducted at the ISIS Centre, a rehabilitation ward of Wakari Hospital (Dunedin, New Zealand), where people with neurological conditions undergo outpatient and inpatient treatment. Participants will be referred by neurologists from the Neurology Department at Dunedin Public Hospital (Southern District Health Board). The ISIS Centre is part of the Southern District Health Board of New Zealand and covers the neurological rehabilitation of 7% of the country's population (~337,000 people).

The inclusion criteria will be:

Aged 18 or olderNew or returning patients presenting to the participating Neurology DepartmentDiagnostic investigations by a neurologist including the appropriate medical examination have been completed.Diagnostic investigations resulted in a diagnosis of FNSD with abnormal movement according to diagnostic criteria of DSM-5 (1) or of a PMD according to the diagnostic criteria by Gupta and Lang (2). Acute (<6 months) as well as persistent symptom presentations (≥6 months) will be accepted.The symptoms cause clinically significant distress or impairment in social, occupational, or other important areas of daily functioning.

Exclusion criteria will be:

Diagnosis of a complex regional pain syndrome, Dissociative Identity Disorder, or Posttraumatic Stress Disorder of high severity with significant dissociationSevere mental health disorder requiring inpatient mental health treatment or potentially affecting trial participation (e.g., suicidality, acute psychosis, active or extensive self-harm)Receiving concomitant psychological intervention that targets motor symptomsInitiation or change in regimen of psychopharmacotherapy at any time between 4 weeks before baseline assessment and the final follow-up assessmentPresence of significant physical trauma/comorbid health conditions (e.g., significant musculoskeletal injuries, severe respiratory illness) precluding participation in our movement retraining (we will include participants who are diagnosed neurological conditions, as long they have individual symptoms that are considered to have a high degree of certainty that they are functional)Low English language proficiencyInability to provide informed consent to participate in the trial

Functional neurological symptoms are associated with increased rates of comorbid mental health disorders (6). In order to obtain a representative sample, individuals with comorbid mental health conditions (e.g., depression) or other functional (non-motor) symptoms will be included as long as the other condition/symptoms do not require inpatient mental health treatment or potentially affect trial participation (see exclusion criterion b).

### Study Design and Procedure

This is a randomized, parallel group, phase II, assessor-blinded, superiority trial comparing the efficacy of a NH-CBT with an active control intervention in individuals with persistent functional neurological symptoms of motor type. Depending on their symptom status at 16-week follow-up, participants in the control group will be offered a delayed NH-CBT treatment. The study procedure is summarized in Figure 1. This protocol has been developed according to the Standard Protocol Items: Recommendations for Interventional Trials (SPIRIT) (see Supplementary Material) (28).

**Figure 1 F1:**
[figure not shown]
Flow chart of the study procedure and outcome assessments (NH-CBT, Nocebo-Hypothesis Cognitive Behavioral Therapy).

A consultant neurologist will assess participants who are consecutively admitted by the participating Neurology Department using the diagnostic criteria of a FNSD (1) or PMD (2). During the *neurological assessment*, participants will undergo a clinical interview and necessary medical investigations and tests to help establish the diagnosis. The neurological assessment will include an interventional component: the neurologist will give participants a standardized explanation of FNSD/PMD (see *Interventions*). This explanation will follow suggestions by Stone (29). It will include elements such as emphasizing the mechanism of the symptom rather than the cause, explaining how the diagnosis was made, reassuring participants that their symptoms are common, emphasizing the reversibility of their symptoms, and introducing self-help as a key component of a successful treatment. It will be explained how depression and anxiety affect and can perpetuate their motor symptoms. Neurologists will be encouraged to use metaphors as part of their explanations. Individuals who appear to be eligible to participate in the trial will then be informed by the neurologist about the trial. The neurologist will seek participants' permission to be contacted by the principal investigator (MR) to attend the psychological assessment.

The first part of the *psychological assessment* is a clinical interview where the principal investigator (MR) will provide individuals interested in participating with more detailed information about the study. We will explain to potential participants that we will offer them one of two treatments: one is conventional and more commonly used for individuals with FNSD, and has been found to be effective; and the other is new, and we are yet to establish evidence of its efficacy. Participants will be blinded to details of the content and proposed mechanisms of NH-CBT and the control treatment, and to differences between both treatments. They will only be informed that the core component of both treatments will be movement retraining, delivered by a rehabilitation professional. During the first part of the psychological assessment we will assess whether individuals meet all eligibility criteria and will ask them to give written consent to participate. In the second part, an assessor who is independent of this study and trained in applying the assessment tools will do the *baseline assessment*. The research assistant will do the Simplified Functional Movement Disorder Rating Scale (S-FMDRS) (30), the Functional Mobility Scale (FMS) (31) and the 10 m-Walk Test (32) with the participant. A physiotherapist will be present to ensure the safety of the participant. Participants will complete a baseline questionnaire including questions about demographic variables and all other outcome measures (see *Outcomes and Assessments*).

Participants will then be randomly assigned to receive either NH-CBT or the active control treatment over the following 8 weeks. At the end of the intervention period (*8-week follow-up*) participants will attend another assessment with an independent, blinded assessor and will complete all outcome measures. Sixteen weeks after baseline, participants from both groups will complete all outcome measures again (*16-week follow-up*). At that point, participants in the control group who have not achieved symptom remission will be offered NH-CBT and will be asked to complete a final questionnaire after 8 weeks of treatment (*24-week follow-up*).

The authors have planned qualitative interviews at the post-therapy stage with the first 10 patients from either arm of the trial, plus all patients identifying as Māori, to elucidate participants' experiences of their treatment and understanding of their symptoms, and to investigate the acceptability and feasibility of the trial processes and cultural influences on patients perception of treatment.

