These epidemiological characteristics highlight the urgent need for effective treatments. FNSD or PMD is one of the most common diagnoses of new referrals to neurological services (8), however over 50% of these individuals do not improve or even feel worse at follow-up (9). There is currently no Class I evidence supporting the efficacy of any treatment for functional motor symptoms (10). The most promising evidence seems to come from cognitive behavioral therapy (CBT) and physiotherapy (11, 12). The central goal of CBT is to identify and modify dysfunctional thinking patterns (e.g. ingrained core thoughts about oneself or one's body, somatic misinterpretations), linked to the motor symptoms, and to promote behavioral changes. For example, typical CBT strategies include psychoeducation (e.g., understanding mechanisms of symptoms), functional behavioral analysis of symptom triggers, taking control of movements, and training of assertive communication (13). In a pilot randomized controlled trial (RCT), participants who underwent CBT tailored for functional motor symptoms significantly improved in daily functioning and secondary outcomes (14). The central goal of physiotherapy is motor reprogramming (15). Usually a systematic strategy is adopted that involves re-establishing elementary movements in affected body regions and reinforcing normal movement, while ignoring abnormal movements. More complex motor tasks are added as soon as individuals are able to perform simple movements appropriately, incrementally approximating normal movement.

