	*NH-CBT movement retraining with video feedback (2–23 sessions)*: The participant is then given opportunities to physically experience themselves as functioning better. The movement retraining is individualized, according to participants' symptoms and needs. The intervention manual proposes exercises for different forms of functional motor symptoms (e.g., functional weakness, balance, tremor, abnormal gait/jerks/myoclonus/involuntary movements, or fixed dystonia). The exercises function as behavioral experiments, to demonstrate to participants that their brains and bodies are capable of working better/normally under certain circumstances. This variability is interpreted to be almost always a sign that there is no damage or disease causing the symptoms. Therapist and participants repeatedly reflect that any improvements can only be due to a change of belief, thus strongly suggesting that belief is the mechanism behind the symptoms. *Distraction:* Distraction, or varying participants' attention to other stimuli, is an important principle of the NH-CBT movement retraining and is almost always the way to create this momentarily improved functioning. A distractor is previously selected collaboratively by therapist and participant (e.g., their favorite music) and is presented whilst participants engage in relevant physical movement. *Video recording/feedback*: Another important element of the NH-CBT movement retraining is video recording and immediate video feedback if the participant shows improved movement when distracted. Improved functioning seen on video feedback is framed as evidence that the “nocebo hypothesis” is valid: symptoms are not caused by structural neurological damage and their bodies are more capable than participants previously believed. More physical activity is then attempted, with further video feedback, and this treatment cycle is repeated, attempting more, and more complex activity as the participant improves. *Purposeful optimism:* Throughout treatment, therapists will be specifically instructed to portray as much optimism as possible to the participant about potential recovery, e.g., talking about how many people have got better using this treatment.	*Control movement retraining (2–23 sessions)*: The movement retraining part of the control intervention is based on a sequential motor learning approach proposed by a consensus recommendation for physiotherapy for functional motor disorders (16). The main rationale for movement retraining is that FNSD/PMD can be conceived of as unwanted patterns of movement that have been subconsciously programmed and learned, and are outside the person's control. It is assumed that these patterns cause symptoms and that symptoms are perpetuated by secondary changes. Movement can be retrained/“reprogrammed” by utilizing a sequential approach to re-establishing more normal movement patterns. *Assessment:* The assessment includes determining levels of falls risk, methods of keeping the person safe, observation of the impact of symptoms on posture and movement, exploring the nature of symptoms, evaluation of any potential compensatory strategies, and exploring possible secondary physical changes. *Sequential approach to restore normal movement patterns*: Elementary symptom free components of movement are established, and built on in successive stages to gradually reshape normal movement patterns. Another target is to change maladaptive compensatory habitual postures, movement patterns, and behaviors. Finally, secondary changes (e.g., physical changes such as deconditioning or changes of social/occupational roles) are addressed. Different movement retraining strategies are provided for different forms of functional motor symptoms in the treatment manual. Therapists are asked to avoid mentioning concepts such as nocebo/placebo effects, beliefs, or expectations. No visual feedback (neither video nor mirror feedback) is used. External distractors (e.g., music, irrelevant conversation) to vary participants' attention are not allowed. Purposeful optimism should not be part of therapists' approach.

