##### Supportive Counseling and Movement Retraining (Active Control Intervention)

The control intervention was designed to control for the non-specific effects of (a) education about symptoms, (b) emotional support from a therapist, and (c) movement retraining. For (a), the psychologist will reassure the participant that symptoms are not caused by structural damage or a degenerative process, however there will be no conversation about beliefs or expectations being an important factor in the development and maintenance of functional motor symptoms. The concept of a nocebo effect will not be mentioned. The psychologist will mainly repeat the explanation of FNSD/PMD by Stone (29) that will have already been provided by the neurologist during the initial neurological assessment. For (b) the psychologist will provide supportive counseling about the participants' symptoms and associated distress and everyday impact, and strategies to manage distress such as relaxation exercises. For (c), motor symptoms will be conceived of as learnt patterns of movement that are outside participants' control. The movement retraining will attempt to re-establish normal movement patterns, but without video feedback and distraction techniques.

The active control intervention will not address any of the key treatment strategies of NH-CBT. The active control intervention will differ from the NH-CBT regarding the following aspects:

It will not include any discussion of the concept of the “nocebo effect” or the role of beliefs as mechanisms of functional motor symptoms.The movement retraining will not be used in the sense of a behavioral experiment, but as a systematic attempt to re-establish normal movement.It will not involve any means of visual feedback.It will not use any engrossing, external distractors, such as music, video, video games, irrelevant conversation, or counting. The only redirecting of attention will involve a suggestion that the participant focus on a point in space, instead of on their bodies.

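### The two treatments are described unequally before randomisation and optimism is instructed in one arm only, so participant expectancy is neither controlled nor measured for a self-reported primary outcome

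*Protocol article*

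**What the plan says.** **Information before consent.** Under Study Design and Procedure (psychological assessment), all potential participants are told that "one is conventional and more commonly used for individuals with FNSD, and has been found to be effective; and the other is new", and of the new treatment that "we are yet to establish evidence of its efficacy". This comes before consent, baseline assessment and randomisation. The same paragraph limits what they learn: "Participants will be blinded to details of the content and proposed mechanisms of NH-CBT and the control treatment, and to differences between both treatments".

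**State of the evidence.** The Introduction says: "There is currently no Class I evidence supporting the efficacy of any treatment for functional motor symptoms".

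**Conduct of therapists.** Table 1, TIDieR item 4, says for NH-CBT that "therapists will be specifically instructed to portray as much optimism as possible to the participant about potential recovery", with the example of "talking about how many people have got better using this treatment". The control column says: "Purposeful optimism should not be part of therapists' approach".

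**Purpose of the control.** "The control intervention was designed to control for the non-specific effects of (a) education about symptoms, (b) emotional support from a therapist"; movement retraining is the third element. The section then lists four aspects in which the control differs from NH-CBT. Optimism is not one of them, nor is it among the four key NH-CBT strategies.

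**Outcome and checks.** The primary outcome is SF-36 Physical Functioning at week 8. Participants complete it themselves. Table 2 marks only the S-FMDRS, the 10 m-Walk Test and the FMS as blinded assessor ratings. Methods for Minimizing Bias has the outcome assessor, not the participant, guess the allocation. Table 2 lists no rating of treatment expectancy or credibility.

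**The concern.** The trial rests on the idea that expectations, including those supplied from outside, can produce and change symptoms (Introduction, on the nocebo effect). The plan itself supplies two such messages. The first, at consent, ranks the treatments by evidence and favours the conventional one. The second, during therapy, is required in NH-CBT and excluded from the control. The primary outcome is the participant's own report, so blinding the assessor does not protect it.

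Two things are at stake. A difference at week 8 could be read as support for the four NH-CBT principles when optimism contributed to it. A small or absent difference could partly reflect NH-CBT participants believing that they had the unproven treatment. With no measure of expectancy or perceived allocation listed, the results could not show whether either happened.

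**Working it through.** **1. The planned effect, reproduced.** Inputs from Sample Size, Power Calculations, and Interim Analyses: f = 0.10 for the group-by-time interaction, m = 3 measurements, r = 0.5, alpha 0.05, power 0.80; two groups.

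- Noncentrality: λ = f² · N · m / (1 − r) = 0.01 × 164 × 3 / 0.5 = 9.84.
- Degrees of freedom: (2 − 1)(3 − 1) = 2 and (164 − 2) × 2 = 324.
- Power is 0.805 at N = 164 and 0.7998 at N = 162, so the stated 164 reproduces.
- Allowing 5% dropout, 164 / 0.95 = 172.6; the plan recruits 172.

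**2. The planned effect in SD units.** If the between-group difference is (0, d, d) or (0, d, 0) at baseline, week 8 and week 16, the interaction effects have mean square d²/18. Hence d = f · √18 = 0.10 × 4.243 = 0.424 SD at week 8. If the difference instead grew linearly, the week-16 difference would be 0.10 × √24 = 0.490 SD and the week-8 difference half of that, 0.245 SD.

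**3. An expectancy shift against that effect.** The documents give no size for such a shift; 0.1 to 0.2 SD is an assumption.

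- Against 0.424 SD: 0.10 / 0.424 = 24% and 0.20 / 0.424 = 47%.
- Against 0.245 SD (linear growth): 0.10 / 0.245 = 41% and 0.20 / 0.245 = 82%.

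**4. Effect on the week-8 test.** Normal approximation, N = 164, r = 0.5, one two-sided test at 0.05, interim looks ignored. SE = √(4/N · (1 − r²)) = √(4/164 × 0.75) = 0.135 baseline-adjusted, or √(4/N · 2(1 − r)) = √(4/164 × 1) = 0.156 for change scores.

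Rejection rate if the only difference between the arms is the shift:

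| Net shift (SD) | Baseline-adjusted | Change scores |
|---|---|---|
| 0 | 5.0% | 5.0% |
| 0.05 | 6.6% | 6.2% |
| 0.10 | 11.5% | 9.8% |
| 0.20 | 31.5% | 24.9% |

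Power for a true 0.424 SD if the net shift favours the control:

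| Net shift (SD) | Baseline-adjusted | Change scores |
|---|---|---|
| 0 | 88% | 78% |
| 0.10 | 67% | 55% |
| 0.20 | 38% | 30% |

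**5. Direction.** The consent message favours the conventional arm, but only among participants who work out which treatment they have. Therapist optimism favours NH-CBT. An NH-CBT participant who hears how many people have recovered with the treatment might even take it for the established one. The net sign cannot be derived from the documents.

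**6. Can participants infer allocation?** NH-CBT includes a nocebo worksheet, a nocebo-based formulation and video feedback. The control education mainly repeats what the neurologist has already said. Inference is plausible, but nothing in the document shows how common it would be, and nothing listed measures it.

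**The case against.** The other side has a strong case, and most of it stands.

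- **Optimism is treatment content.** Table 1 names it as an NH-CBT procedure and states its exclusion in the parallel control column. The aim is to learn whether NH-CBT beats an active control, which is a comparison of packages. This stands: the randomised comparison is not invalidated.
- **The control never claimed to equalise expectancy.** A reader might infer that it was meant to. The article names only education, emotional support and movement retraining, so expectancy is left uncontrolled; no promise is broken.
- **The messages do not strictly contradict each other.** A reader might see a contradiction between unproven efficacy at consent and therapists saying that people got better. The earlier uncontrolled case series, with reliable and significant change in 7 of 12 episodes, makes both statements possible. Likewise, a lay statement that conventional treatment works can coexist with a lack of Class I evidence, since the Introduction cites promising smaller studies. The weakness is the unequal ranking, which sits uneasily with the article's own reading of the evidence.
- **The consent message is common to both arms.** It precedes randomisation, and participants are not told how the treatments differ. This stands: an arm difference needs inferred allocation. If participants did infer it, this message alone would favour the control, which is conservative for a superiority claim but costs power.
- **Safeguards exist.** Three blinded assessor outcomes are collected at each main visit, and qualitative interviews are planned. These help, but the interviews cover the first 10 patients and those identifying as Māori, and the assessor ratings are secondary outcomes.
- **Disclosing that a treatment is unproven is honest.** It is, and equal wording can keep that disclosure.

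**Conclusion.** The point holds as a low-cost improvement. The treatments are described unequally before randomisation, optimism is instructed in one arm and excluded from the other, and the self-reported primary outcome has no listed check on expectancy or perceived allocation. The size is unknown: on an assumed net shift of 0.1 to 0.2 SD it is about 24% to 47% of the planned 0.42 SD, or 41% to 82% if the planned effect accrues linearly to week 16. The sign is also unknown.

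Two stronger readings are not supported. A reader might conclude that the trial is biased towards NH-CBT; the messages oppose each other, so no direction follows. A reader might also conclude that the primary comparison is unsound; it remains a valid estimate of the NH-CBT package, optimism included. What it cannot support is attribution of an effect to the four listed principles alone.

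**What to change.** 1. **Consent wording.** Describe the treatments equally: two treatments, both centred on movement retraining, neither yet firmly established, and not known which works better. This still tells participants that efficacy is uncertain.
2. **Measurement.** Add a brief credibility/expectancy rating after the initial education session and a participant allocation guess at week 8, in both arms. Report both by arm, and read the S-FMDRS, FMS and 10 m-Walk Test alongside the primary result.
3. **Description of the arms.** Name optimism in the section on key strategies and differences as a component that differs between the arms, and word conclusions for the whole package.

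The cost is an amendment to the consent script, a few extra self-report items and a narrower mechanistic claim. Therapy content, sample size and the primary analysis do not change.
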